### Endpoints

The primary composite effectiveness endpoint, aligned with previous PFA trials (eg, ADVANTAGE AF^14^^,^^15^), is defined as acute ablation success and freedom from clinically meaningful treatment failure during the postblanking monitoring period (from the end of an 8-week blanking period to 12 months). Treatment failure is defined as a composite of documented AF/atrial flutter/AT (≥30 seconds on ambulatory monitoring or ≥10 seconds on 12-lead ECG), repeat ablation, electrical cardioversion, or initiation/escalation of class I/III antiarrhythmic drugs including amiodarone. Secondary endpoints include the individual components of the primary endpoint, time to documented AF recurrence, AF burden based on rhythm-monitoring data, change in quality of life (Atrial Fibrillation Effect on Quality-of-Life and EQ-5D-5L), and predefined safety outcomes including stroke or transient ischemic attack, cardiac tamponade/pericarditis, major vascular complications, and major bleeding. Phrenic nerve injury (symptomatic or asymptomatic) will also be prospectively collected and adjudicated as a prespecified safety outcome. Additional late safety surveillance (eg, PV stenosis and atrioesophageal fistula) will be captured as prespecified AEs and serious AEs. Exploratory analyses will evaluate posterior wall block durability in relation to recurrence, trajectories of hemolysis biomarkers and renal function, and prespecified subgroup effects (Table 3). Full endpoint definitions and ascertainment are presented in Supplemental Table 2. In cases of repeat ablation, remapping data (PV reconnection and posterior wall conduction status, when assessed) will be captured in the electronic data capture and analyzed exploratorily.

**Table 3 tbl3:** Primary, secondary, and exploratory endpoints

Category	Endpoints
Primary effectiveness endpoints	Acute ablation success and freedom from the following during the postblanking monitoring period (from the end of an 8-wk blanking period through 12 mo), defined as a composite of: 1) Documented AF/AFL/AT (≥30 s on ambulatory monitoring or ≥10 s on 12-lead ECG) 2) Repeat ablation for AF/AFL/AT 3) Electrical cardioversion for AF/AFL/AT 4) Initiation/escalation of class I/III antiarrhythmic drugs including amiodarone
Key secondary endpoints	1) Individual components of the primary composite endpoint 2) Time to documented AF recurrence 3) AF burden based on rhythm-monitoring data 4) Change in quality of life: AFEQT and EQ-5D-5L 5) Safety outcomes (see Supplemental Table 2 for definitions)
Exploratory endpoints	1) Association between posterior wall block durability and recurrence 2) Trajectories of hemolysis biomarkers and renal function 3) Prespecified subgroup effects (age, sex, BMI, LAD, AF duration, DR-FLASH score)

Overview of study endpoints. Detailed endpoint definitions and ascertainment procedures are presented in Supplemental Table 2.

AF = atrial fibrillation; AFEQT = Atrial Fibrillation Effect on Quality-of-Life; AFL = atrial flutter; AT = atrial tachycardia; BMI = body mass index; ECG = electrocardiography; LAD = left atrial diameter.

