### Follow-up and rhythm monitoring

Patient follow-up will consist of outpatient visits at 3, 6, and 12 months after the index ablation (day 0), including clinical assessment, review of medications, and 12-lead ECG at each visit. The use of antiarrhythmic drugs during follow-up will be systematically recorded in both treatment groups regardless of initiation or dose adjustment. Rhythm monitoring will include protocol-mandated 24-hour Holter monitoring at 6 and 12 months. In addition, transtelephonic monitoring and symptom-triggered recordings will be performed using an Omron portable ECG device (HCG-8060T), which will be provided by the study team. Participants will be instructed to transmit recordings biweekly after discharge and additionally at the time of symptoms suggestive of arrhythmia. Portable ECG transmissions are intended to complement intermittent Holter monitoring and improve capture of clinically relevant recurrences in real-world follow-up.

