Effectiveness analyses will be conducted according to the intention-to-treat principle. Safety analyses will be performed in all participants who received study treatment (safety set). For the primary composite effectiveness endpoint, time-to-event analyses will focus on the postblanking treatment failure component; acute ablation success will be summarized descriptively by group. Time-to-event outcomes will be analyzed using Kaplan–Meier methods and compared with the log-rank test; hazard ratios and 95% confidence intervals will be estimated using Cox proportional hazards models, with prespecified covariate adjustment as appropriate. Rhythm endpoint documentation will be reviewed by the blinded arrhythmia core laboratory, and major safety outcomes will be adjudicated by the independent CEC. Prespecified subgroup analyses (age, sex, body mass index, LAD, AF duration, DR-FLASH score^19^) will be assessed using treatment × subgroup interaction terms. Missing data will be handled primarily by complete-case analysis, with multiple imputation and sensitivity analyses considered if missingness is substantial, as specified in the statistical analysis plan. A single interim review is planned after approximately 1 year of enrollment and will be conducted blinded under the oversight of an independent data and safety monitoring board. No formal interim hypothesis testing for effectiveness is planned. Analyses will be performed using SAS software (version 9.4 or later, SAS Institute Inc, Cary, NC).

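### A repeat ablation in weeks 0-8, or a class I/III drug started or escalated then and continued, is scored as success if no later event occurs

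*Protocol article*

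**What the plan says.** Under Endpoints, the protocol article defines effectiveness as acute success plus "freedom from clinically meaningful treatment failure during the postblanking monitoring period (from the end of an 8-week blanking period to 12 months"). Table 3 repeats the window ahead of its numbered list, "freedom from the following during the postblanking monitoring period (from the end of an 8-wk blanking period through 12 mo"), so it governs every component: documented arrhythmia, "Repeat ablation for AF/AFL/AT", "Electrical cardioversion for AF/AFL/AT" and the drug component. No exception is given for events inside the blanking period. Statistical considerations confirms that the time-to-event analysis concerns post-blanking failure, with acute success only described by group.

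Table 3 names the arrhythmia indication for repeat ablation and cardioversion but not for drugs: "3) Electrical cardioversion for AF/AFL/AT 4) Initiation/escalation of class I/III antiarrhythmic drugs including amiodarone".

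The early data will exist. Under Follow-up and rhythm monitoring, "The use of antiarrhythmic drugs during follow-up will be systematically recorded in both treatment groups regardless of initiation or dose adjustment". Under Endpoints, remapping data at repeat ablation are to be captured electronically. The trial is open-label, and the blinded core laboratory is described as assessing rhythm endpoints from ECG documentation.

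**The concern.** Blanking is normally there so that early arrhythmia after ablation is not read as failure. Here it also removes two signs that the index strategy was judged insufficient: a second procedure, and a new or intensified antiarrhythmic drug that continues. A patient who is arrhythmia-free from week 8 because of either is credited to the randomised arm as if the index procedure had sufficed.

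For repeat ablation, this touches the contrast under test. The Ablation procedures section rules out posterior wall ablation in the PVI-alone group when describing the index procedure. No text shown sets a matching limit for a redo. A PVI-alone patient could therefore receive posterior wall lesions in week 6 and be analysed under intention to treat as a PVI-alone success.

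For drugs, the same prescription is scored in opposite ways according to its start date: begun in week 4 and continued, success; begun in week 9, failure.

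Both decisions rest with unblinded physicians, so their frequency and timing may differ by arm.

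**Working it through.** **1. Following the rule as written** (no other event from week 8 to month 12)

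| Patient | Counted in the window? | Score |
|---|---|---|
| Repeat ablation for AF/AFL/AT, week 6 | No | Success |
| Repeat ablation for AF/AFL/AT, week 10 | Yes | Failure |
| Class I/III drug started week 4, continued to month 12 | No, the start precedes the window | Success |
| Same drug started week 9 | Yes | Failure |

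**2. The plan's sample size.** Inputs from Statistical considerations: success 60% and 72.5%, two-sided alpha 0.05, power 80%. With the pooled two-proportion formula,

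n = [1.960·√(2p̄q̄) + 0.842·√(p₁q₁ + p₂q₂)]² / d²,

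where p̄ = 0.6625, q̄ = 0.3375 and d = 0.125:

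- 1.960 × √0.4472 = 1.3107
- 0.842 × √0.4394 = 0.5579
- (1.3107 + 0.5579)² / 0.015625 = 223.5, so 224 per group

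This matches the plan. Dividing by 0.9 gives 249, against 250 planned. The sample size is not in error.

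**3. Effect of hidden failures on power.** Assumption: 60% and 72.5% are the rates when early re-treatment counts as failure, and a stated share of each arm's patients moves to success under the rule as written. The share is net: patients who have a later event are failures either way. The article gives no rates.

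Power = Φ[(d − 1.960·√(2p̄q̄/224)) / √((p₁q₁ + p₂q₂)/224)]

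For 3% of PVI-alone only, success is 63% against 72.5% and d = 0.095. Then (0.095 − 0.0866)/0.0439 = 0.19, and Φ = 0.58. For 5% of PVI-alone only, (0.075 − 0.0858)/0.0437 = −0.25, and Φ = 0.40.

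| Hidden, PVI alone | Hidden, PVI + PWI | Observed difference (points) | Power |
|---|---|---|---|
| 0 | 0 | 12.5 | 80% |
| 3% | 0 | 9.5 | 58% |
| 5% | 0 | 7.5 | 40% |
| 5% | 2% | 9.5 | 59% |
| 0 | 3% | 15.5 | 94% |
| 5% | 5% | 12.5 | 84% |

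Three per cent of 224 is about 7 patients and 5% is about 11.

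**4. No true effect.** Take true success of 60% in both arms and an assumed 3-point shift between them (58.5% and 61.5%). The null standard error is √(0.48/224) = 0.0463, so the critical difference is 0.0907. The upper tail is 1 − Φ[(0.0907 − 0.03)/0.0463] = 0.095 and the lower tail about 0.005. Two-sided type I error is therefore about 10% instead of 5%.

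**The case against.** Four points can be made for the plan.

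- **Full definitions lie elsewhere.** The article refers to Supplemental Table 2, which is not shown and might add a rule for early events or an indication for drugs. This stands as a caution. It does not dispose of the point, because the article itself states the window for all four components without exception.
- **The blanked composite is deliberate.** It is described as aligned with earlier PFA trials to allow cross-trial reading. That is a fair reason to keep it as primary. It does not settle what an early redo should mean in a randomised comparison of two lesion sets, and a sensitivity analysis costs no comparability.
- **The rates are assumed.** This stands in full. The plan sets 60% and 72.5% for its composite as written, whereas the working treats them as rates under the alternative scoring. Equal shares leave the difference intact.
- **An unchanged pre-ablation drug would still pass.** True, but the plan's drug component concerns initiation and escalation, not drug-free status. The proposed scoring keeps that logic.

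Two stronger readings are tempting. A reader might infer from Table 3 that a drug change after week 8 counts for any reason. Only initiation or escalation counts, Supplemental Table 2 may name an indication, and eligibility (persistent AF, no history of ventricular tachycardia or fibrillation) leaves few other reasons to start such a drug. A reader might also infer that the three treatment components escape adjudication and that masked committee review would cure the bias. Statistical considerations says "major safety outcomes will be adjudicated by the independent CEC", but the oversight section gives the committee clinical events as well, without saying whether these treatments are included. Masked review could confirm why a treatment was given; it cannot remove bias from the unblinded decision to give it.

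**Conclusion.** The point holds as a scoring problem. Applied as written, the endpoint counts as success a patient whose freedom from arrhythmia may owe to a second ablation, or to a continuing drug begun, in weeks 0-8. This can inflate success in both arms, and it biases the comparison if early re-treatment differs by arm.

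Neither direction nor size can be fixed from the article. More hidden failures in the PVI-alone arm dilute a true benefit; more in the PVI + PWI arm exaggerate it. The power range of about 58-40% rests on assumed shares of 3 to 5% in the PVI-alone arm only, and the type I error of about 10% on an assumed 3-point shift. They show sensitivity to a handful of patients and are not forecasts.

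The missing qualifier on component 4 is a smaller inconsistency within Table 3, subject to Supplemental Table 2. The planned sample size is correctly computed.

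**What to change.** In the endpoint definition and Table 3:

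1. Score repeat ablation for AF/AFL/AT from day 0 as failure.
2. Score a class I/III drug started or escalated during blanking and still in use after week 8 as failure, dated at the end of blanking.
3. Add the AF/AFL/AT qualifier to component 4, to match components 2 and 3, unless Supplemental Table 2 already does so.

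Blanking stays for arrhythmia recordings and cardioversion. If the blanked composite is retained as primary for comparability with earlier PFA trials, prespecify items 1 and 2 as a sensitivity analysis of the primary endpoint.

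The cost is endpoint wording, slightly lower success rates in both arms if the primary definition changes, and one more analysis if it does not. Drug use and repeat-ablation data are already to be collected. Patient treatment is unaffected; only scoring changes.

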### Statistical considerations

Sample size was informed by previous randomized trials of PWI using thermal energy sources (eg, STAR AF II,^3^ CAPLA,^4^ and other studies^5^^,^^17^^,^^18^), in which the 1-year freedom from atrial arrhythmia after PVI alone ranged from approximately 53% to 71% and incremental benefit of routine PWI was not consistently demonstrated. In contrast, contemporary PFA technology may enable more durable and safer posterior wall lesion sets, which could translate into improved clinical effectiveness.

Based on published PFA outcomes and supporting prospective data,^14^^,^^15^ the assumed 12-month freedom from the primary composite effectiveness endpoint was set at 60% for the PVI-alone group and 72.5% for the PVI + PWI group (absolute difference 12.5%). With a 2-sided type I error probability of .05 and 80% power, 224 participants per group (total 448) are required. To account for an anticipated 10% dropout rate, the planned enrollment is 250 participants per group, resulting in a total sample size of 500.

Effectiveness analyses will be conducted according to the intention-to-treat principle. Safety analyses will be performed in all participants who received study treatment (safety set). For the primary composite effectiveness endpoint, time-to-event analyses will focus on the postblanking treatment failure component; acute ablation success will be summarized descriptively by group. Time-to-event outcomes will be analyzed using Kaplan–Meier methods and compared with the log-rank test; hazard ratios and 95% confidence intervals will be estimated using Cox proportional hazards models, with prespecified covariate adjustment as appropriate. Rhythm endpoint documentation will be reviewed by the blinded arrhythmia core laboratory, and major safety outcomes will be adjudicated by the independent CEC. Prespecified subgroup analyses (age, sex, body mass index, LAD, AF duration, DR-FLASH score^19^) will be assessed using treatment × subgroup interaction terms. Missing data will be handled primarily by complete-case analysis, with multiple imputation and sensitivity analyses considered if missingness is substantial, as specified in the statistical analysis plan. A single interim review is planned after approximately 1 year of enrollment and will be conducted blinded under the oversight of an independent data and safety monitoring board. No formal interim hypothesis testing for effectiveness is planned. Analyses will be performed using SAS software (version 9.4 or later, SAS Institute Inc, Cary, NC).

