Acute PVI success and PWI success will be confirmed by demonstration of entrance block with the disappearance of local PV and posterior wall field potentials. Where technically feasible, pacing from the PVs and posterior wall may be performed to assess exit block at the operator’s discretion.

No protocol-mandated waiting period is required, consistent with the pragmatic study design; reassessment after a short waiting period may be performed per operator discretion and site practice. Intracardiac echocardiography and/or fluoroscopic guidance may be used according to site practice and operator preference, and their use will be recorded. Field tag–based contact metrics are available at participating sites and may be incorporated into procedural assessment when feasible using a standardized approach informed by previous field tag–based analyses.^16^ In addition, emerging impedance-based contact sensing technologies may be incorporated as they become clinically available and will be analyzed exploratorily when applicable.

Adjunctive radiofrequency ablation (eg, cavotricuspid isthmus ablation) will be permitted in both groups only for predefined clinical indications, including documented non-PV triggers, sustained AT, typical atrial flutter, or other safety-driven needs; all adjunctive ablation will be recorded in the electronic data capture system. Procedural characteristics, including total procedure time (skin to skin), fluoroscopy time, acute PVI success, acute PWI success (PVI + PWI group only), and the presence and location of adjunctive ablation, will be collected.

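### The primary endpoint requires acute ablation success, but the stated primary analysis covers only the postblanking component, and no test of the full composite is stated

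*Protocol article*

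**What the plan says.** In the Endpoints section, the primary composite "is defined as acute ablation success and freedom from clinically meaningful treatment failure during the postblanking monitoring period". The Abstract, the Figure 1 legend and Table 3 say the same. The failure events are documented atrial arrhythmia plus "repeat ablation, electrical cardioversion, or initiation/escalation of class I/III antiarrhythmic drugs including amiodarone". An unsuccessful index procedure is not one of them.

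Statistical considerations sizes the trial on that composite: "the assumed 12-month freedom from the primary composite effectiveness endpoint was set at 60% for the PVI-alone group", against 72.5% for PVI + PWI. With two-sided 0.05 and 80% power this gives 224 per group, raised to 250 for 10% dropout.

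The same section then fixes the analysis. Effectiveness is to be analysed by intention to treat, but for the primary composite "time-to-event analyses will focus on the postblanking treatment failure component; acute ablation success will be summarized descriptively by group". The between-group methods named are these: "Time-to-event outcomes will be analyzed using Kaplan–Meier methods and compared with the log-rank test", with hazard ratios from Cox models.

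Ablation procedures defines acute PVI success as entrance block in all attempted veins. It lists separately "acute PWI success (PVI + PWI group only".

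**The concern.** The endpoint and the sample size refer to one quantity and the stated analysis to another. The difference lies in one type of patient: no acute success at the index procedure and no documented event between week 8 and month 12. The Endpoints section counts this patient as a failure. The log-rank and Cox analyses count the same patient as event-free.

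This affects the comparison between groups if such patients are unevenly distributed. The PVI + PWI group receives an extra lesion set with its own acute criterion. If acute ablation success in that group includes posterior wall isolation, the group has an additional way to fail, and the stated analysis ignores it. In an open-label trial, which of the two results counts as primary should not be left open until data are available. The Discussion also presents the composite as deliberately comparable with earlier trials of the same system, and a result on the postblanking component alone is not that composite.

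**Working it through.** **1. The plan's own figure.** Inputs from Statistical considerations: p1 = 0.60, p2 = 0.725, two-sided 0.05, 80% power. Pooled two-proportion formula, with mean p = 0.6625:

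n = [1.960 × √(2 × 0.6625 × 0.3375) + 0.842 × √(0.60 × 0.40 + 0.725 × 0.275)]² / 0.125² = 3.491 / 0.015625 = 223.5, so 224 per group.

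This matches the plan. Dropout: 224 / 0.90 = 248.9, so 249, rounded up to 250. A log-rank calculation at the same rates (hazard ratio ln 0.725 / ln 0.60 = 0.630) needs 147 events by Schoenfeld or 152 by Freedman, which is about 218 or 226 per group. The sample size is sound for either method.

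**2. How one patient is classified.**

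| Acute success | Event from week 8 to month 12 | Endpoint as defined | Analysis as stated |
|---|---|---|---|
| Yes | No | Success | Event-free |
| Yes | Yes | Failure | Event |
| No | Yes | Failure | Event |
| No | No | **Failure** | **Event-free** |

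Only the last row differs.

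**3. Size of the difference.** In each group let a be the acute failure rate and e the share of acute failures with no later event. Then

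postblanking freedom = composite success + a × e,

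and the contrast analysed exceeds the composite contrast by (a × e in PVI + PWI) − (a × e in PVI alone).

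The article gives neither a nor e, so the values below are assumptions. The composite is held at 60% and 72.5%, as the sizing text states. The middle columns assume that acute failure is independent of later events, so that postblanking freedom = composite / (1 − a). The last column instead assumes e = 30% in both groups.

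| Acute failure, PVI / PVI + PWI | Postblanking freedom, independence | Difference | Difference if e = 30% |
|---|---|---|---|
| 0% / 0% | 60.0% / 72.5% | 12.5 points | 12.5 points |
| 2% / 2% | 61.2% / 74.0% | 12.8 points | 12.5 points |
| 1% / 3% | 60.6% / 74.7% | 14.1 points | 13.1 points |
| 2% / 5% | 61.2% / 76.3% | 15.1 points | 13.4 points |

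If every acute failure later has an event (e = 0), the two analyses give the same 12-month proportions.

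**4. Power.** On the sizing text's own reading, the 2% / 5% case gives the analysed component about 93% power in a two-proportion comparison at 224 per group, which is more than planned. A loss appears only if 60% and 72.5% are taken as postblanking rates. The composite at 2% / 5% is then 0.98 × 60% = 58.8% against 0.95 × 72.5% = 68.9%, a difference of 10.1 points with power of about 60%. The article does not describe its rates that way.

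**The case against.** **The wording leaves room.** Saying that analyses focus on a component does not exclude a test of the full composite in the statistical analysis plan. This stands, so it cannot be said that the trial never tests its endpoint. But the article does state how its primary endpoint is analysed, and that statement does not match the definition. This is not a detail left to another document.

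**A reader might infer that the trial is underpowered.** The article does not support this. The low power figure requires 60% and 72.5% to be postblanking rates, while the sizing text calls them rates for the composite. It also requires assumed acute failure rates and independence from later events. If acute failures tend to recur, the gap shrinks.

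**A reader might infer that the acute hurdle is higher in the PVI + PWI group.** No text shown says that acute ablation success in the primary endpoint includes the posterior wall. Acute PVI and acute PWI success are listed as separate items, and the full definitions are in a supplement that is not shown. The unequal hurdle is a possibility only.

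**A reader might also object that a randomized patient who is never ablated has no place on the time scale.** The article does not fix the time origin, and handling of untreated patients is ordinary content of an analysis plan. This is no finding.

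**The practical effect may be small.** That is fair. If acute failure is rare or similar in both groups, the two analyses nearly agree. The definition and the analysis still need to name the same quantity.

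**Conclusion.** The inconsistency is real and can be read directly from the text: the endpoint is defined and sized with acute success, the stated analysis leaves it out, and no test of the full composite is given. The direction of any bias depends on which group has more patients without acute success and without a later event. If that is the PVI + PWI group, the stated analysis favours it.

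The size cannot be fixed from the article. Under the assumptions shown, the shift in the 12-month difference runs from nil to about 2.6 points (15.1 − 12.5), the upper end needing 2% against 5% acute failure and independence. With equal rates of 2% it is at most about 0.3 points. Neither an error in the sample size nor a loss of power has been shown.

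**What to change.** Choose one quantity and use it throughout.

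- **Keep acute success in the endpoint.** In Statistical considerations, state that absence of acute success counts as a failure in the primary intention-to-treat analysis, either as an event at the start of the time scale or through a comparison of 12-month composite success proportions. Use one acute criterion in both groups (PVI entrance block), and report acute PWI success separately as a procedural outcome.
- **Or analyse the postblanking component alone.** Remove acute success from the primary endpoint in the Abstract, the Figure 1 legend, the Endpoints section and Table 3, and state that 60% and 72.5% refer to the postblanking component.

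Either is a change of wording, and acute success is already being recorded. Under the first option the reported freedom rates may be slightly lower, and events at time zero fit less well with the proportional hazards model. A comparison of proportions avoids the latter but needs a rule for patients lost before month 12. Under the second option the primary result is no longer the composite that the Discussion describes as harmonized with earlier trials, and that text would need adjusting.

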**Methods:**

PERSIST-PWI is an investigator-initiated, multicenter, open-label, parallel-group randomized controlled trial at approximately 60 sites in Japan. 500 patients with persistent AF (AF duration ≤3 years) will be randomized 1:1 to PVI alone or PVI + PWI. Pre- and postablation 3-dimensional mapping with OPAL HDx (FARAVIEW) is mandated. Follow-up includes visits at 3, 6, and 12 months with 12-lead electrocardiograms (ECGs), 24-hour Holter monitoring at 6 and 12 months, and biweekly plus symptom-triggered portable ECG transmissions.

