### Randomization and stratification

Randomization will be performed centrally using a minimization-based dynamic allocation method. Patients will be allocated 1:1 to the PVI-alone group or the PVI + PWI group, stratified by site, age category (<75 vs ≥75 years), and LAD (<45 vs ≥45 mm). The overall study design is presented in Figure 1.

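### The minimization factors are not carried into the stated log-rank and Cox analyses: a minor gap, closed by naming age and LAD (but not site) as strata or covariates

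*Protocol article*

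**What the plan says.** **Allocation** (Protocol article, Randomization and stratification): "Randomization will be performed centrally using a minimization-based dynamic allocation method", 1:1, "stratified by site, age category (<75 vs ≥75 years), and LAD (<45 vs ≥45 mm". The abstract describes the trial as "open-label, parallel-group randomized controlled trial at approximately 60 sites in Japan".

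**Analysis** (Statistical considerations): time-to-event outcomes are to be "compared with the log-rank test; hazard ratios and 95% confidence intervals will be estimated using Cox proportional hazards models", the latter "with prespecified covariate adjustment as appropriate". In that sentence the adjustment belongs to the Cox models, not to the log-rank test. No covariate is named, and nothing says that the allocation factors are among them.

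**Sample size** (same section): freedom from the primary endpoint "was set at 60% for the PVI-alone group and 72.5% for the PVI + PWI group (absolute difference 12.5" percentage points). "With a 2-sided type I error probability of .05 and 80% power, 224 participants per group (total 448) are required".

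**The concern.** Minimization restricts how far the two groups can differ on its factors. If those factors affect outcome, the treatment estimate varies less from trial to trial than under simple randomization. A log-rank test or Cox model that ignores them still uses a variance that allows for imbalance the design has largely removed. Its test is then somewhat conservative, and a little power is given up. The remedy uses data already collected.

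The text also leaves the opposite choice open. Someone who follows the rule of analysing as randomized to the letter could stratify on all three factors. With about 60 sites that would cost far more than ignoring them.

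**Working it through.** **Inputs from the article:** 60% and 72.5% free of failure at 12 months; two-sided 5% level; 80% power; 224 per group; about 60 sites; two categories each for age and LAD.

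**Assumptions, not in the documents:** 25% of patients aged ≥75; 40% with LAD ≥45 mm; prognostic hazard ratios (HR) of 1.0 to 2.5; between-site SD of 0 to 0.5 on the log-hazard scale; a minimization that follows the balancing arm with probability 0.8; constant hazard; no dropout within the 448.

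**1. The plan's own figure.** Two proportions, pooled variance, mean proportion (0.60 + 0.725)/2 = 0.6625:

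n = [1.960·√(2·0.6625·0.3375) + 0.842·√(0.60·0.40 + 0.725·0.275)]² / 0.125² = (1.311 + 0.558)² / 0.015625 ≈ 223.5, so 224 per group.

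This agrees exactly. Dropout: 224/0.9 = 249, stated as 250. The calculation claims no gain from adjustment, so it does not depend on the point at issue. As a log-rank calculation, HR = ln 0.725 / ln 0.60 = 0.630, which needs 147 events (Schoenfeld) or about 147/0.3375 = 436 patients. That is consistent with the plan.

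**2. Test without strata against test stratified by age × LAD.** Minimization was simulated with N = 448 and the marginal rates held at 60% and 72.5%, 2,500 trials per row:

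| HR age / HR LAD / site SD | Type I error: no strata | Type I error: age × LAD | Power: no strata | Power: age × LAD | Power: site × age × LAD |
|---|---|---|---|---|---|
| 1.0 / 1.0 / 0 | 4.6% | 4.6% | 81.2% | 80.8% | 61.5% |
| 1.3 / 1.5 / 0 | 4.4% | 4.7% | 80.9% | 81.6% | 61.4% |
| 1.3 / 1.5 / 0.3 | 5.0% | 4.9% | 80.3% | 80.6% | 61.6% |
| 1.5 / 2.0 / 0.5 | 4.4% | 4.8% | 82.5% | 83.6% | 64.9% |
| 2.0 / 2.5 / 0.5 | 3.3% | 4.7% | 82.7% | 84.6% | 65.6% |

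Monte Carlo standard error is √(0.8·0.2/2500) = 0.8 points for power and √(0.05·0.95/2500) = 0.4 points for type I error. Differences below about 1 point should not be read as real.

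A separate simulation (450 patients, 60 sites, 80/20 minimization) gave type I error of 3.4% against 4.4% at LAD HR 2.0 and age HR 1.3. At LAD HR 2.5 and age HR 1.5 it gave 3.6% against 4.9%, with power of 80.1% against 82.5%. At LAD HR 1.5 the difference was negligible. The direction is the same. At LAD HR 2.0 the two sets differ on how conservative the test is (3.4% and 4.4%), so the size there is uncertain.

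**3. Cross-check through the standard error.** Under the null in the last row, the unadjusted Cox model reports a mean standard error of 0.1502 while the estimates actually vary with SD 0.1409. The ratio is 1.066, about 7% too wide. The implied type I error is 2·[1 − Φ(1.96·1.066)] = 2·[1 − Φ(2.09)] ≈ 3.7%, in line with the simulated 3.3%. In the moderate rows the excess is 1% to 4%. An SD from 2,500 runs carries a relative error of 1/√5000 = 1.4%, so much of that is noise.

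**4. Does adjustment shorten the Cox interval?** In the last row under the alternative, the mean model standard error of the log HR is 0.1663 unadjusted and 0.1666 adjusted, so it does not. The mean log HR moves from −0.468 to −0.497. The gain comes from an estimate further from zero.

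**5. Site as a stratum.** 60 × 2 × 2 = 240 cells, so 448/240 = 1.9 to 500/240 = 2.1 patients per cell. Many cells then hold no comparison between arms. Power falls to 61% to 66%, which is 17 to 20 points below the test without strata. Site alone as the stratum gives 77% to 81%.

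**The case against.** The strongest reply is that this is a condensed article, that a statistical analysis plan exists but is not shown, and that log-rank strata and Cox covariates usually belong there. That stands as a limit on the point. A reader might infer that the primary test is definitely unstratified, but the article never says so. It names no strata, and the unseen plan may supply them. The point stays because the same section lists all six subgroup variables, including age and LAD, and refers missing-data handling to the analysis plan by name. For the main comparison it offers only a loosely worded adjustment, attached to the Cox model.

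A reader might also infer that covariates could be chosen after the data are seen. The text does not support that, since it says the adjustment is prespecified. The weakness is narrower: the qualifier that follows leaves open whether the allocation factors are included.

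The reply also says that harm is small and depends on assumed prognostic strength. That stands in full. So does the observation that the article nowhere proposes site as a stratum. The loss under full stratification is a reason to word the fix carefully, and is not a fault of the plan.

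**Conclusion.** The point holds as a minor, cost-free improvement. Allocation uses three factors, and the analyses as stated are not tied to any of them. If age and LAD are prognostic, a test without strata has a type I error of about 3.3% to 5.0% and gives up about 0 to 2 points of power over assumed HRs of 1.0 to 2.5. At an LAD HR of 1.5 or below the effect is negligible. These figures rest on the assumptions listed above. The direction is secure, but the size is not known from the documents.

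Two stronger conclusions are tempting and do not follow. One is that the trial is underpowered: the test without strata reached 80.1% to 82.7% in every scenario with a reported power figure, and any error is conservative, so false positives are not inflated. The other is that adjustment would give tighter hazard-ratio intervals: on the log-HR scale it does not. The adjusted HR is a conditional estimate, and the benefit is a log HR further from zero and a test size closer to nominal.

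**What to change.** State in Statistical considerations, or confirm that the statistical analysis plan already states:

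> The primary log-rank test is stratified by age (<75, ≥75 years) and LAD (<45, ≥45 mm). The Cox model is stratified by, or adjusted for, the same two factors. Site is not used as a stratum together with them; it is handled as a random (frailty) effect or in a sensitivity analysis. The log-rank test without strata is reported as a sensitivity analysis.

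This fixed list replaces the open qualifier on covariate adjustment. The report should say that the adjusted hazard ratio is conditional on age and LAD category. The frailty option was not simulated here and is offered as a standard way to allow for site without splitting the data into very small cells.

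Cost: wording only. No new data, patients or change in sample size.
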